#### Primary qualitative outcomes

Qualitative content analysis following principles of the framework approach will be undertaken for outcome (A) recruitment [73, 74]. To develop an analytical framework, two researchers will read through all answers from Microsoft Excel spreadsheet charts and will apply inductive “open coding” (i.e. label what they consider to be relevant from as many perspectives as possible). After coding the first transcripts, the labels applied will be compared between the two researchers to agree on a set of codes and these codes will be grouped to form themes and categories. The analytical framework, including the codes and themes, will consequently be used to index all transcripts. Data will be summarized by category and put into a Microsoft Excel spreadsheet chart to generate a matrix. The chart consists of participants (rows) and emergent qualitative themes (columns) and will be used to identify similarities and differences between participants’ expressed thoughts. The qualitative findings will be described in detail, supported by quotes from participants.

#### Secondary outcomes

Although the aim of this pilot trial is to assess the feasibility and acceptability of running a definitive trial, the secondary psychological, behavioral and biological outcomes will be analyzed to mimic the definitive trial. All analyses of the secondary outcomes will hence be viewed as preliminary and thus interpreted with caution.

Outcomes will be analyzed per-protocol and by intention to treat (ITT). For the per-protocol analysis, participants who are found ineligible after randomization or deviated from the probiotics/placebo product intake (i.e. less than 80% intake) will be excluded from the main analysis. For the ITT analysis, all randomized participants, regardless of protocol adherence or dropouts (i.e. participants who withdraw consent for continued follow up), will be included in the main analysis. Participants will be analyzed according to the group to which they were originally allocated. In case of missing data, missing values will be imputed. Student’s *t* test will be used to analyze normally distributed data and the nonparametric Mann–Whitney U test will be used to analyze non-normally distributed data. For comparisons of more than two groups (e.g. differences in the relative abundance of bacteria at the level of phylum up to the level of order in microbial samples), analysis of variance with Tukey’s post-hoc test of the intervention and placebo group at the primary endpoint will be compared using a one-way analysis of covariance (ANCOVA) model, where the covariate will be the baseline score. In addition, the effect size will be computed to estimate the required sample size for the future large-scale trial. The significance level for statistical analysis is set at *p* < 0.05.

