## Methods

### Trial design

This probiotic intervention project in mothers and their infants is a double-blind, randomized pilot trial (RCT) (probiotic intervention versus placebo). Forty healthy pregnant women (≥ 18 years of age) with at least mild depressive symptoms and/or anxiety in the late second/third trimester of an uncomplicated pregnancy (≥ 26 and ≤ 30 weeks gestation) will be enrolled in this study (see Fig. 1). Participants will orally consume a probiotic multispecies mixture (Ecologic® Barrier; 2,5 × 10^9^ colony forming units (CFU)/g per dosage; daily dosage 2 g) once daily, or a placebo, for 8–14 weeks consecutively (depending on the time of delivery). Detailed information on the intervention components is provided under “Intervention procedures”. For more information on the protocol items, please refer to the Standard Protocol Items: Recommendations for Interventional Trials (SPIRIT) checklist (Additional file 1).

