### Sample size calculation

The main aim of the PIP pilot trial is to evaluate the feasibility and acceptability of a probiotic intervention in pregnant women suffering from depressive and/or anxiety symptoms. Since the pilot study will lay the basis for designing a larger RCT, the sample size calculations are based on a full RCT. An a priori power analysis to estimate the sample size was conducted using G*Power 3.1. An effect size of *f* = 0.187 was used for the sample size calculation, based on the prior studies of Benton (2007) [26] examining the effect of probiotics on symptoms of depression in healthy volunteers with elevated levels of depression. With a significance level of 5% and power of 80%, including 60 women per arm (total of 120) would be required to examine probiotic effectiveness in reducing depressive symptoms. To account for dropout, poor compliance, antibiotic use around the time of the intervention period and pregnancy complications, all of which may negate any potential effects from the probiotic/placebo product, we estimate that a total of 150 women would be needed for a full trial. Since the primary aim of the present pilot trial is to examine feasibility and acceptability, recruiting a total of 40 women (20 women per arm (~ 27% of a full trial)) would be adequate for this outcome. No interim analysis of preliminary results will be conducted given the expected relatively short duration of the pilot study and given that the study is labeled as minimal-risk research.

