### Randomization, blinding and treatment allocation

The 40 women will be randomly allocated to either the probiotic arm or placebo arm. A computer random number algorithm (1:1 allocation ratio) at Winclove probiotics B.V. will randomize women, using blocks of 4. A staff member at Winclove Probiotics B.V., who is not involved in the study, will sequentially label probiotic boxes (including number sachets with the probiotic or placebo product). The staff member will also create a sealed randomization list and sealed code break envelopes per participant in order to keep the trial investigators unaware of the allocation sequence and randomization code, and to maintain blinding until the end of the pilot trial. The randomization code will not be released until the last participant has finished the pilot trial. The CI, who is unaware of participant assignment in the allocation sequence, will distribute the sequentially numbered probiotic boxes. Participants will be assigned to a numbered box upon order of providing informed consent. Next to investigators, the participants, care providers and outcome assessor are blinded to the participant’s allocation. The Principal Investigator (PI) has access to the randomization data in case it is necessary to unblind. The blind may be broken for a serious and unexpected event, if it is essential for the medical management of subjects, or may provide critical safety information about the intervention that could have implications for the ongoing conduct of this trial. Sealed code break envelopes per participant are accessible within 24 h. In the event of a code break, the name of the code breaker, the signature and the date and time will be recorded on the outside of the envelope.

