Maternal lifestyle	Smoking (yes/no)	Baseline value	Proportion of participants smoking
	Alcohol (yes/no)	Baseline value	Proportion of participants drinking alcohol
Pregnancy characteristics	Occurrence of infections during pregnancy	Final value	Proportion of participants reporting infections (i.e. influenza, fever, diarrhea) throughout the study
Delivery characteristics	Gestational age	Final value	Gestational age at delivery
Pregnancy and delivery complications	Number of pregnancy and delivery complications (i.e. hypertensive disorders of pregnancy (pregnancy induced hypertension, preeclampsia, eclampsia, hemolysis - elevated liver enzymes - low platelet count (HELLP) syndrome), gestational diabetes mellitus, preterm birth, cesarean section, retention placentae, hemorrhage postpartum, small or large for gestational age (birth weight < p10 or > p90), puerperal fever, prolonged labor, premature rupture of membranes)	Final value	Proportion of participants diagnosed with pregnancy or delivery complications at delivery
Infant antibiotic use	Number of antibiotics used	Final value	Proportion of infants receiving antibiotics during first month of life
Depression	Edinburgh Postnatal Depression Scale (EPDS) score	Change from baseline to t1 and t4	Mean (SD)/median (IQR)
Depression/cognitive reactivity	Leiden Index of Depression Sensitivity-Revised (LEIDS-R) score	Change from baseline to t1 and t4	Mean (SD)/median (IQR)
Pregnancy related anxiety	Pregnancy Related Anxiety Questionnaire-Revised (PRAQ-R) score	Change from baseline to t1	Mean (SD)/median (IQR)
General anxiety	State-trait Anxiety Inventory (STAI-S) score	Change from baseline to t1 and t4	Mean (SD)/median (IQR)
Pregnancy-related daily hassles	Pregnancy-related daily hassles (PES) score	Change from baseline to t1 and t4	Mean (SD)/median (IQR)
General daily hassles/stress	Daily Hassles List (APL) score	Change from baseline to t1 and t4	Mean (SD)/median (IQR)
Mother to infant bonding	Maternal Antenatal Attachment Scale (MAAS) score	Change from baseline to t1	Mean (SD)/median (IQR)
	Maternal Postnatal Attachment Scale (MPAS)	Change from t3 to t4	Mean (SD)/median (IQR)
Biological samples	Maternal fecal samples (microbiota)	Change from baseline to t1	Relative abundance and diversity of bacteria at phylum up to genus level
	Maternal vaginal samples (microbiota)	Change from baseline to t1	Relative abundance and diversity of bacteria at phylum up to genus level

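### Two analyses compete for the same two-arm comparison, the baseline-adjusted one is tied to an undefined primary endpoint, and bacterial taxa are treated as groups

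*Protocol article*

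**What the plan says.** The relevant text is in the protocol article, Statistical analysis, Secondary outcomes.

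- Normally distributed data get Student's t test; for the rest, the Mann-Whitney U "test will be used to analyze non-normally distributed data". No covariate is named.
- The next sentence opens with comparisons of more than two groups, giving as its example "differences in the relative abundance of bacteria at the level of phylum up to the level of order in microbial samples". It assigns these to analysis of variance with Tukey's procedure and runs on, without a break, into "post-hoc test of the intervention and placebo group at the primary endpoint will be compared using a one-way analysis of covariance (ANCOVA) model". The covariate is the baseline score.
- The section then says that an effect size will be computed to size the later large trial. It also says that the secondary outcomes are analysed so as to imitate that trial and are to be read as preliminary.

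Table 2 sets the participant-level metric. It is change from t0 to t1 and t4 for EPDS, LEIDS-R, STAI-S, PES and APL, and change from t0 to t1 for PRAQ-R, MAAS, maternal microbiota and hair cortisol. MPAS and infant microbiota are changes from t3 to t4, and infant crying is a final value. For maternal microbiota the table gives "Relative abundance and diversity of bacteria at phylum up to genus level".

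**The concern.** Three things do not fit together.

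First, the t test (or Mann-Whitney) and the ANCOVA both address the same contrast, "probiotic intervention versus placebo", and no rule says which governs a given outcome. Second, the ANCOVA is attached to an endpoint that the article does not define. Third, a two-arm trial has no comparison of more than two groups of women, and the example given makes bacterial taxa the groups.

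The effect estimate is meant to inform the size of the full trial. A change-score test and an ANCOVA give estimates of different precision and standardised effects of different size, so the planning figure depends on which one is meant. The microbiota test, as exemplified, would not answer the protocol's question of whether the probiotic changes maternal or infant microbiota.

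**Working it through.** **1. What the ANCOVA could refer to.** There are two candidates.

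| Candidate | Where | Fits a baseline-score ANCOVA? |
|---|---|---|
| The pilot's primary outcomes: recruitment, retention, compliance, experiences | Primary outcome; Table 1 | No. They are analysed descriptively and have no baseline score |
| The full trial's primary outcome: anxiety and depressive symptoms in pregnancy | Primary outcome, second paragraph | Yes, but no scale or time point is fixed. Table 2 offers EPDS, LEIDS-R and STAI-S at t1 and t4, and PRAQ-R at t1 |

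The second is the sensible reading, but it leaves several possible analyses.

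**2. The plan's own sample-size figure.** The inputs, from Sample size calculation, are an effect size f where "0.187 was used for the sample size calculation", 5% significance, 80% power, and 60 women per arm (120 in total). For two equal groups d = 2f = 0.374. With two-sided 5%, n per arm = 2 × (1.960 + 0.842)² / 0.374² = 112.2, so 113 per arm or 226 in total (228 by the exact F calculation). A plain two-group comparison with 120 women has about 53% power. Totals near 120 do arise under settings that the article does not state, such as three repeated measures with correlation 0.3 (122) or ANCOVA with correlation 0.7 (118). The figure therefore neither settles which model was intended nor can be called wrong on this evidence.

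**3. What the choice of analysis is worth.** Let ρ be the correlation between the t0 and follow-up values, with equal variance σ² at both times. ρ is not in the article, so 0.3, 0.5 and 0.7 are assumed.

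- Variance factor for a change score: 2(1 − ρ)
- Variance factor for ANCOVA: 1 − ρ² (ignoring the one degree of freedom spent on the covariate)
- Ratio, ANCOVA to change: (1 − ρ²) / [2(1 − ρ)] = (1 + ρ)/2
- Relative width of the confidence interval: √[(1 + ρ)/2]

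| | ρ = 0.3 | ρ = 0.5 | ρ = 0.7 |
|---|---|---|---|
| Variance ratio | 0.65 | 0.75 | 0.85 |
| Confidence interval narrower by | 19% | 13% | 8% |
| Standardised effect, change score: 0.374/√[2(1 − ρ)] | 0.316 | 0.374 | 0.483 |
| Standardised effect, ANCOVA: 0.374/√(1 − ρ²) | 0.392 | 0.432 | 0.524 |
| n per arm for 80% power, change: 112.2 × 2(1 − ρ) | 158 | 113 | 68 |
| n per arm for 80% power, ANCOVA: 112.2 × (1 − ρ²) | 103 | 85 | 58 |

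The same raw difference thus leads to different full-trial sizes according to the model.

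**4. Chance imbalance.** The pilot plans on "recruiting a total of 40 women (20 women per arm" and so on, so the baseline difference between arms has SD √(2/20) = 0.316 in baseline SD units. A change-score contrast does not carry all of this. The part left in the estimate is (1 − ρ) × 0.316, an SD of 0.22, 0.16 or 0.09 at the three correlations. ANCOVA removes that part.

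**5. Taxa as groups.** Allocation is to two arms at a "1:1 allocation ratio". Each sample yields the relative abundance of many taxa, which are dependent because they are shares of one whole. ANOVA across taxa assumes independent groups, and Tukey's pairwise contrasts would be taxon against taxon. Neither is a contrast of probiotic with placebo. The level named in the example (order) also differs from the genus level in Table 2, while the Discussion singles out lactobacilli and bifidobacteria.

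**The case against.** The strongest reply is that baseline is already used twice: through the change-score metric of Table 2 and through the ANCOVA. The awkward sentence is probably two sentences run together, with the ANCOVA meant for the full trial's symptom outcome, which is the first secondary objective here. The analyses are labelled preliminary, no success criteria are set for them, and the pilot's primary results are unaffected. Much of this stands, and it rules out several stronger readings that a reader might infer:

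- *That symptom outcomes are tested with no use of baseline.* Table 2 makes change from baseline the metric. What the t test and Mann-Whitney lack is baseline as a covariate.
- *That chance imbalance biases the estimates.* Over randomisations the change-score estimate is unbiased. Imbalance affects precision and the error in a particular sample, and the 0.316 in the working is the raw baseline difference, not the error that remains.
- *That ANCOVA is missing for the symptom scales.* It may well be intended for them. The gap is that neither scale nor time point is named.
- *That the microbiota analysis stops at order.* That level appears only inside an example, so this is a wording mismatch with Table 2 to reconcile.

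What the reply does not remove is the absence of any rule between the two analyses when one of them is to supply the planning effect size. Nor does it rescue the example of taxa as groups. Both are things the article states, not details left to an analysis plan.

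**Conclusion.** The point holds as a defect of specification that should be corrected. The article sets out two analyses for one contrast, leaves the endpoint of the better one undefined, and gives a multi-group procedure that has no place in a two-arm comparison.

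The cost of using change scores where ANCOVA is possible is precision. ANCOVA needs 0.65 to 0.85 of the variance, so 40 women would inform the estimate about as well as 62, 53 or 47 would on change scores (40/0.65, 40/0.75, 40/0.85). These figures rest on assumed correlations of 0.3 to 0.7 and equal variances at both times. They apply only to outcomes that have a t0 value and for which ANCOVA is not already intended. There is no such gain for infant crying, MPAS or infant microbiota. The feasibility and acceptability outcomes are untouched.

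The taxa point needs no assumed figure. As exemplified, the test does not compare the arms.

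**What to change.** Rewrite the paragraph as follows.

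- For every continuous secondary outcome with a t0 value, make ANCOVA (follow-up value on arm and t0 value) the main analysis, at the time points listed in Table 2. Report the adjusted mean difference with its 95% confidence interval.
- Replace the reference to a primary endpoint with the named scale or scales and time point.
- Take the effect size for the full trial from this model, and state the standard deviation used as its denominator.
- Keep two-group tests for outcomes without a t0 value: infant crying, MPAS and infant microbiota. The t3 value of the last two is taken after the intervention, so it is not a baseline.
- Drop ANOVA with Tukey. Compare each taxon between the two arms as a separate outcome, to the genus level of Table 2, with adjustment for multiple testing and for the t0 value where one exists. The transformation and the multiplicity method can be left to the analysis plan.

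The cost is a change of analysis wording. According to Trial status, 35 women had consented and 18 had completed at submission, so data collection was still under way. The change asks for no measurement beyond those already scheduled.

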#### Secondary outcomes

In addition to the primary objective, this pilot trial includes six secondary objectives to ensure that certain data can be collected and to exploratorily assess whether maternal probiotic intake, compared to placebo, potentially has an effect on (1) depressive and/or anxiety symptoms, (2) maternal stress (i.e. reported and hair cortisol), (3) maternal vaginal and intestinal microbiota, (4) maternal bonding to offspring, (5) infant microbiota and (6) infant crying. In the absence of a core outcome set to measure potential effectiveness of probiotics on maternal mood, we choose outcome measures that have shown good psychometric properties and have been previously used to assess depressive symptoms, anxiety and stress in RCTs including non-pregnant [6, 28] and pregnant women [36]. Similarly, outcome measures used to assess maternal bonding to offspring and infant crying have been shown reliable in previous studies [36–38]. Regarding the rationale for the choice of biological outcomes, please see “Discussion”. Given that the main aim of this pilot trial is to assess feasibility and acceptability, and not probiotic effectiveness, no criteria will be set for comparison of treatment success between the two treatment arms (probiotic versus placebo) for any of the secondary outcomes. Figure 1 shows the secondary outcomes measured throughout the study. Table 2 displays the secondary outcome measurement variables, participant level analysis metric and methods of aggregation at specific measurement time points of interest. Participants will fill in all questionnaires electronically, except for the Baby’s Day Diary, in order to improve data accuracy and the timelines for receiving data. For data collection forms (instructions and CRFs) see Additional file 2A-E.

**Table 2 Tab2:** Secondary outcome measurement variables, participant level analysis metric and methods of aggregation at specific measurement time points of interest

Secondary outcome	Measurement variable	Participant-level analysis metric^a^	Method of aggregation for each probiotic/placebo treatment arm
Demographic information	History of atopy (mother)	Baseline value	Proportion of participants with positive history of atopy at baseline
	History of atopy (father)	Baseline value	Proportion of fathers with positive history of atopy at baseline
	History of psychiatric disorders	Baseline value	Proportion of participants with positive history of depression or anxiety disorder at baseline

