### Infant microbiota and crying

Maternal prenatal depression or anxiety does not only affect the mother, but also her infant. Maternal prenatal probiotic intake, by improving maternal mood, may be beneficial for the infant in improving infant intestinal microbiota and reducing infant crying. For instance, maternal prenatal stress has been related to changes in infant intestinal microbiota [55] and increased crying behavior in infants [104–106]. Infants of mothers with high levels of prenatal stress were found to have higher relative abundance of pathogenetic bacteria and lower relative abundance of beneficial bacteria (i.e. lactobacilli and bifidobacteria), compared to mothers with low levels of stress [55]. Increased levels of pathogenic intestinal bacteria and reduction in beneficial bacteria have been associated with excessive crying in infants [38]. Hence, we postulate that symptoms of maternal prenatal anxiety or depression may cause intestinal microbial imbalances in infants, and that this in turn may contribute to excessive crying.

To date, most studies have focused on the effects of probiotics on maternal mood during the postnatal period [6, 14]. No studies have examined the effects of probiotics on maternal mood during pregnancy. If a probiotic intervention during pregnancy is shown to be feasible and acceptable, combined with preliminary results indicating plausible effectiveness to improve maternal prenatal mood, evaluating of the effectiveness of probiotics on maternal prenatal mood in a large RCT would be warranted.

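### An effect size from about 20 women per arm is too imprecise to size the full trial, and the article is inconsistent on whether an efficacy signal counts towards going ahead

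*Protocol article*

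**What the plan says.** **Use of the pilot estimate.** Statistical analysis, Secondary outcomes: "In addition, the effect size will be computed to estimate the required sample size for the future large-scale trial". The same section sets a general level for the secondary analyses ("The significance level for statistical analysis is set at *p* < 0.05") and asks that these analyses be treated as preliminary and read with caution.

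**Existing full-trial size.** Sample size calculation: "An effect size of *f* = 0.187 was used for the sample size calculation", taken from an outside study. It continues: "With a significance level of 5% and power of 80%, including 60 women per arm (total of 120) would be required". After an allowance for losses, "we estimate that a total of 150 women would be needed for a full trial". The pilot's size is justified by its feasibility and acceptability aim: "recruiting a total of 40 women (20 women per arm (~ 27% of a full trial)) would be adequate for this outcome". Dropouts are not replaced (Primary outcomes: quantitative).

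**Progression.** Measurements and outcomes, Secondary outcomes: "no criteria will be set for comparison of treatment success between the two treatment arms", for any secondary outcome. The criteria in Table 1 cover recruitment, retention, compliance and participants' experience. The Discussion (Infant microbiota and crying) says that a large trial would be warranted if the intervention proves feasible and acceptable, "combined with preliminary results indicating plausible effectiveness to improve maternal prenatal mood".

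**The concern.** A sample of 40 chosen to measure recruitment, retention and compliance is given a second task, estimating a treatment effect well enough to plan the next trial. Required sample size varies with the inverse square of the effect, so modest error in the effect becomes very large error in the size. The definitive trial could be planned far too small, or so large that it is abandoned.

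The Discussion sentence adds a selection problem. If the full trial goes ahead only after an encouraging estimate, the estimates that reach the planning stage are on average too large, and the trials planned from them too small. Because the efficacy condition is undefined and sits beside a statement that no such criteria exist, its role could be settled after the data are seen.

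**Working it through.** **Inputs.** From Sample size calculation: f = 0.187, 5% level, 80% power, 60 per arm, 150 after losses, pilot of 20 per arm. Assumed here: two-sided testing, since sidedness is not stated.

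**The plan's own figure.**
- Read as a plain two-group comparison, f = 0.187 is d = 2 × 0.187 = 0.374. A noncentral F calculation then needs 228 women in total, and 120 women give 53% power.
- About 120 is reached under designs that the article does not specify, for example ANCOVA with a baseline correlation near 0.69, or a between-group comparison over three measurements correlated at 0.3 (122). So 120 is not reproduced from the stated inputs, but it cannot be called wrong.
- 120 / (1 − 0.20) = 150, so the implied loss is 20%. 40 / 150 = 27%, as stated.

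**Two assumed true effects.** The rest is done for both readings.
- d = 0.516, at which 60 per arm gives 80% power. It also approximates the baseline-adjusted case: 0.374 / √(1 − 0.69²) = 0.517.
- d = 0.374, the plain two-group reading.

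**Precision at 20 per arm.** SE(d) = √(2/20 + d²/80), which is 0.321 for d = 0.516 and 0.319 for d = 0.374. An observed 0.516 has a 95% CI of −0.12 to 1.14; an observed 0.374 has −0.25 to 1.00. Power is 36% and 21% respectively. With 16 per arm (20% loss) it is 29% and 18%.

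**Planned size from the pilot estimate.** n per arm = 2 × (2.8016 / d)², rounded up. The true needs are 2 × (2.8016 / 0.5157)² = 59.03, so 60 per arm and 120 in total; and 2 × (2.8016 / 0.374)² = 112.2, so 113 per arm and 226 in total. Results from 200,000 simulated pilots of 20 per arm (noncentral t):

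| | True d = 0.516 | True d = 0.374 |
|---|---|---|
| True total need | 120 | 226 |
| Wrong sign, no usable size | 5% | 12% |
| Planned total, median* | 108 | 176 |
| Planned total, 10th–90th percentile* | about 36–940 | about 48–2,360 |
| True power below 80%* | 53% | 57% |
| True power below 50%* | 26% | 35% |

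*Among pilots with the right sign.

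About half the plans would fall below 80% power with any roughly unbiased estimate. The spread, and the share below 50%, are the more telling rows.

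**Effect of selection.** Dropping only the wrong-sign pilots already puts the median below the true need (108 against 120; 176 against 226). As a strict illustration, the smallest significant estimate is 2.024 × √(2/20) = 0.64. It gives 2 × (2.8016 / 0.64)² = 38.3, so 39 per arm and 78 in total. Significant pilots average d = 0.87 when the truth is 0.516, and 0.84 when it is 0.374.

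**What the pilot can supply.** With 38 degrees of freedom, the 95% limits for the pooled SD are 0.82 to 1.29 times its estimate. At a fixed target difference the size scales with SD², so it moves by 0.82² = 0.67 to 1.29² = 1.66. That is wide, but usable.

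**The case against.** The strongest reply is that the article already limits these analyses. It calls them exploratory and preliminary, and it asks for caution. It speaks of estimating a sample size, not of fixing one. An external figure of 120 or 150 already stands, and nothing says that the pilot's estimate replaces it. A later trial would need its own justification. All of this stands, and it lowers the severity. It does not remove the point: caution in interpretation does not correct a formula fed with a noisy effect, and the only use stated for the pilot effect size is that formula.

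It can also be objected that an unadjusted calculation with d = 0.374 is the unfavourable case, given that ANCOVA on the baseline score is mentioned. That is fair, and so the case consistent with the plan's own 60 per arm is shown beside it. The conclusion is the same under both.

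A reader might infer several stronger things that the documents do not support:
- That significance at 0.05 is the test for going ahead. The level is a general one for the secondary analyses, and the Discussion sentence has no threshold. Under the Table 1 footnote, even a missed criterion only leads to revisions being considered.
- That the many secondary comparisons have a calculable chance of a false positive. Fifteen independent null comparisons would give 1 − 0.95^15 = 54%, but these are overlapping scales measured in the same women, and positive correlation would lower the figure.
- That most significant secondary results would be chance findings. This depends on how many effects are real, which the documents do not say.

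**Conclusion.** The point holds for the planned use of the effect size. With 20 women per arm, the planned full-trial total would range about 26-fold between its 10th and 90th percentiles (940 / 36) if the true d is 0.516, and about 49-fold (2,360 / 48) if it is 0.374. Over half of the plans with the right sign would be underpowered. These figures assume a two-sided 5% level, 80% power, complete data on all 40 women, and one or other of the two true effects. Losses would widen the spread.

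The inconsistency on progression also holds. The Discussion counts a sign of effectiveness, while the outcome section and Table 1 do not. The bias towards too small a trial arises only if progression is in fact made to depend on a promising estimate, which the Table 1 criteria do not require.

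It does not follow that the article's 120 is wrong, that the pilot estimate will displace it, or that a p-value decides progression. Severity is should-fix: the pilot's primary outcomes, conduct and validity are untouched, and the risk falls on the planning of the next trial.

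**What to change.** 1. In Statistical analysis, Secondary outcomes, delete or replace the sample-size sentence. State that the full trial will be sized on a pre-stated important difference in depressive or anxiety score, and that the pilot supplies only nuisance parameters: the pooled SD with its confidence limit, the baseline-to-t1 correlation, attrition and compliance.
2. Report the secondary outcomes as between-arm differences with 95% confidence intervals, labelled exploratory. Whether the 0.05 level is also kept is largely a matter of preference.
3. Reconcile the Discussion sentence on effectiveness with the statement that no success criteria are set and with Table 1, so that progression rests on the stated feasibility and acceptability criteria.

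The cost is a few sentences. Data collection and pilot size do not change. The sponsor gives up a pilot-based effect size for planning and has to name and defend an important difference instead.
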